#### Relevant concomitant care permitted or prohibited during the trial {11d}

In accordance with the exclusion criteria for the study, participation in an interdisciplinary obesity training for the duration of 1 year or more other than the STARKIDS program and participation in a child rehabilitation or inpatient treatment for weight loss are prohibited during the trial. Beyond these exclusions, implementing the structured face-to-face and e-health supported STARKIDS intervention or structured standard care will not require alteration to all other usual care pathways (including use of any medication) and these will continue for both trial arms.

#### Provisions for post-trial care {30}

Not applicable, since ancillary and post-trial care is provided within the standard care.

### Outcomes {12}

All outcomes are measured on three measurement time points: (T0) at baseline/inclusion in the study, (T1) baseline + 12 months, and (T2) baseline + 18 months. T1 marks the primary outcome measurement time point and T2 marks the secondary outcome measurement time point.

#### Primary outcomes

There are two hierarchically structured primary outcomes: an objective parameter measuring weight development as the main primary outcome and a subjective parameter measuring self- and parent-reported quality of life of the children and adolescents. Weight development is measured from baseline to follow-up in BMI standard deviation scores (BMI-SDS or BMI *z*-scores) that are derived using the LMS method [20] (BMI-SDS_LMS_) with a representative German reference population [21, 22]. The (hierarchically structured) second primary outcome is a positive change of mean in children’s and adolescents’ quality of life from baseline to follow-up [23]. Primary outcomes are assessed at each of the three measurement points in the pediatric practice (BMI-SDS_LMS_) or online via a questionnaire (quality of life).

#### Secondary outcomes

Secondary outcomes originate from a questionnaire which are answered at the three main measurement points and most commonly analyzed as change from baseline. Most variables are assessed twice: once in the parent perspective and once as an own perspective by children aged twelve and older. The secondary outcomes are structured around the main modules of the STARKIDS program. Table 2 contains a detailed overview of outcomes according to intervention modules including their psychometric properties. In summary, the following topics are covered:“Eating and drinking”: dietary intake, rhythm of dietary intake, eating behavior, and knowledge about diet.“Activity and media”: mount and style of physical activity, reasons/aims, and barriers for/to physical activity and support in physical activity. In the field of media consumption, parental mediation, attitudes towards advertising, parent-child conflict and the duration of media consumption are measured and analyzed.“Family life”: psychological variables of interest are disruptive behaviors in children and adolescents, family climate, shared activities, sleep, eating disorder symptoms, body dissatisfaction, stress, and family coherence.

**Table 2 Tab2:** Overview of the questionnaire instruments according to the thematic modules of the STARKIDS intervention

Questionnaire	No. of items	Subscales	Reliability	Validity	Completer (about)
*Overall*					
Quality of Life Questionnaire for children (KINDL^R^), with obesity module *Original title: Fragebogen zur Erfassung der gesundheitsbezogenen Lebensqualität bei Kindern und Jugendlichen (KINDL*^*R*^*)* [23, 25–27]	24 plus 16 (obesity module)	Physical well-being, psychological well-being, self-esteem, family, friends, functioning in school/kindergarten	Cronbach’s *a* = .85	Convergent validity: parent report: *r* = .44–.63; child report: *r* = .33–.59 correlation with SDQ	Parent (child) Adolescent (self)
University of Rhode Island Change Assessment (URICA-S) [28]	16	Precontemplation, contemplation, action, maintenance	Cronbach’s *a* = .61–.84	n/a	Adolescent (self)
Parent Perspective University of Rhode Island Change Assessment -Short (PURICA-S) [24]	16	Precontemplation, contemplation, action, maintenance	Cronbach’s *a* = .30–.84	Criteria validity good to very good (exception subscale precontemplation)	Parent (self)
*Eating and drinking module*					
Dutch Eating Behavior Questionnaire – Children (DEBQ-C) [29]	20	Restraint eating, emotional eating, external eating	Cronbach’s *a* = .74–.81	n/a	Parent (child) Adolescent (self)
Rhythm of dietary intake	2		n/a	n/a	Parent (child) Adolescent (self)
Knowledge about nutrition	10				Parent (self) Adolescent (self)
Food Frequency Questionnaire (FFQ) – KiGGS version [30, 31]	114		n/a	*r* = .22–.69 correlation with DISHES nutrition interview	Parent (child) Adolescent (self)
*Activity and media module*					
MoMo-Physical-Activity-Questionnaire *Original title: Aktivitätsfragebogen des Motorik-Moduls* (MoMo-AFB, selected items) [32]	20		Intraclass correlation (ICC): *r* = .68	*r* = .29 correlation with accelerometer data	Parent (child) Adolescent (self)
Physical Activity, Exercise, and Sport Questionnaire *Original title: Bewegungs- und Sportaktivität Fragebogen* (BSA-F) [33]	10	Sports activity and physical activity	n/a	*r* = .32 with VO_2_max	Parent (self)
Physical Activity Enjoyment Scale (PACES) [34]	16		Cronbach’s *a* = .89–.93	*r* = .42 correlation with physical activity diary	Parent (child) Adolescent (self)
Self-concordance of sport- and exercise-related goals scale *Original title: Sport- und Bewegungsbezogene Selbstkonkordanz Skala* (SSK) [35]	12	Intrinsic, identified, introjected and extrinsic modes of motivation	Cronbach’s *a* = .70–.82	*r* = .25–.38 correlation with physical activity	Parent (child) Adolescent (self)
Basic Psychological Needs Questionnaire *Original title: Fragebogen zu Psychologischen Grundbedürfnissen*	9	Autonomy, relatedness, competence	n/a	n/a	Parent (child) Adolescent (self)
Exercise-related Support - Family *Original title: Sportbezogene Unterstützung aus der Familie (SU-F)* [36]	6		Cronbach’s *a* = .85	n/a	Parent (child) Adolescent (self)
Exercise-related Support - Friends *Original title: Sportbezogene Unterstützung von Freunden und Bekannten (SU-B)* [36]	5		Cronbach’s *a* = .89	n/a	Parent (child) Adolescent (self)
Barriers to physical activity	4		n/a	n/a	Parent (child) Adolescent (self)
Bernese Motive and Goal Inventory *Original title: Berner Motiv- und Zielinventar* (BMZI) [37]	26	Contact, competition/performance, distraction/catharsis, body/appearance, health, fitness, esthetics, and risk/challenge	Test-retest: .62–.83	Discriminant validity for acceptable	Parent (child) Adolescent (self)
Parental mediation [38–42]	51	Active parental mediation, restrictive parental mediation, social co-viewing/co-use, supervision, concept-oriented family consumer communication, socio-oriented family consumer communication	Cronbach’s *a* = .75–.94	n/a	Parent (self)
Attitudes towards advertising [38, 43]	7		Cronbach’s *a* = .80	n/a	Parent (self)
Parent-Child Conflict [42, 44]	3		Cronbach’s *a* = .69	n/a	Parent (self)
Duration of media consumption	2		n/a	n/a	Parent (child) Adolescent (self)
*Family life module*					
Strength and Difficulties Questionnaire (SDQ) [45, 46]	25	Emotional problems, striking behaviors, hyperactivity, troubles with peers, pro-social behaviors	Cronbach’s *a* = .55–.77 (self-evaluation)	n/a	Parent (child) Adolescent (self)
Family climate (items of the iFamily study) [47–49]	8		Cronbach’s *a* = .61–.83	n/a	Parent (self) Adolescent (self)
Shared activities (items of the iFamily study) [47, 49]	6		n/a	n/a	Parent (self) Adolescent (self)
Sleep (items of the KiGGS study) [50]	4		n/a	n/a	Parent (child) Adolescent (self)
Eating Disorder Examination Questionnaire 8 (EDEQ-8) [51]	8		Cronbach’s *a* =.93	*r* = .75 correlation with EAT-13	Parent (self)
Child version of the Eating Disorder Examination Questionnaire 8 (ChEDEQ-8) [52]	8		Cronbach’s *a* = .89	*r* = -?.65 correlation with body esteem scale	Adolescent (self)
Eating Disorder Inventory (EDI-2), subscale body dissatisfaction [53–55]	9	Only one scale used (body dissatisfaction)	Cronbach’s *a* = .84–.89 *r*_*tt*_ = .89/.94 (subscale)	*r* = .35 correlation with Beck Depression Inventory (subscale)	Parent (self)
Eating behaviors inventory – child, subscale dissatisfaction with body *Original title: Inventar zum Essverhalten und Gewichtsproblemen – Kind (IEG-K)* [56]		Only one scale used (body dissatisfaction)	Cronbach’s *a* = .88 (subscale)	n/a	Adolescent (self)
Weight Bias Internalization Scale (WBIS) [57, 58]	11		Cronbach’s *a* = .87 *r*_*tt*_ = .88 (8 weeks)	*r* = .2 for BMI-SDS *r* = -?.7 for self-esteem *r* = -?.77 for HRQoL (weight), acceptable construct validity in CFA	Adolescent (self)
Modified Weight Self Stigma Questionnaire (WSSQ) [59]	13	Modification of original scale to assess stigma by association	Cronbach’s *a* = .87 for original scale	*r* = -?.47 for HRQoL (weight)	Parent (self/child)
Body Image Avatars [60, 61]	3		These ratings have never been used before, for similar 2D avatars, a sample with female adult participants found *r*_*tt*_ = .88–.90 (5 weeks)	Rating corresponds with actual BMI: *r* = .89	Parent (child) Adolescent (self)
Parenting Self-efficacy questionnaire *Original title: Fragebogen zur Selbstwirksamkeit in der Erziehung* (FSW) [62]	9		Cronbach’s *a* =.78/.79	*r* = .63/.64 with parent behavior in risk situations	Parent (self)
Self-efficacy scale *Original title: Skala zur Allgemeinen Selbstwirksamkeitserwartung* (SWE) [63, 64]	10		Cronbach’s *a* =.78–.79	n/a	Adolescent (self)
Perceived Stress Questionnaire-20 (PSQ-20) [65]	20	Worries, tension, joy, demands	Cronbach’s *a* =.80–.86	*r* = -?.58 correlation with WHOQOL-Bref (global)	Parent (self)
Systemic Clinical Outcome and Routine Evaluation-15 (SCORE-15) [66]	15		Cronbach’s *a* = .89	Convergent validity shown by correlation with various measures	Parent (self) Adolescent (self)
*Socioeconomic outcomes*					
Mannheimer Modul RV (MRV), adaptation for STARKIDS	31		n/a	n/a	Parent (child) Adolescent (self)

*BMI-SDS* BMI standard deviation score, *CFA* confirmatory factor analysis, *EAT-13* Eating Attitudes Test – short version, *HRQoL* health-related quality of life, *n/a* not available, *WHOQOL-Bref* World Health Organization Quality of Life questionnaire, *VO*_*2*_*max* maximal oxygen consumption

#### Other outcomes

In addition to the aforementioned outcomes, demographic and physiological variables such as somatic diseases related to overweight and obesity and blood levels as well as motivational stages according to [name] et al. [24] are assessed. In addition, data of serious games and reflection tools provided by the e-health platform will be analyzed to complement the questionnaire data. For the health economics perspective, outcomes are costs and preference-based measures to elicit quality-adjusted life years (QALYs) as well as routine data from the statutory health insurance company AOK Baden-Wuerttemberg of invoiced health services.

### Participant timeline {13}

The participant timeline is presented in Fig. 1.

**Fig. 1 Fig1:**
[figure not shown]
Participant timeline and schedule of enrollment, interventions, and assessments

### Sample size {14}

A total sample size of 1000 children and adolescents from 100 pediatric practices (on average 10 in each pediatric practice, with high variability of cluster sizes) was determined. This is based on a power calculation that takes dropout (adherence rate of 75%) and a cluster effect of 2 into account. With the projected final sample (750 individuals in 100 clusters), differences in proportions of participants that reach the target criterion (i.e., − 0.2 BMI-SDS_LMS_ reduction) between 14% (27% vs. 13%) and 17% (58.5 vs. 41.5%) are detectable with a maximum type I error rate of 5% and minimal power of 80% in a *χ*^2^ test.

### Recruitment {15}

In order to reach the target sample size, the recruitment of the current study is organized in collaboration with the participating health insurance company as well as the association of pediatricians of the state of Baden-Wuerttemberg. First, pediatric practices are recruited. All eligible pediatric practices are informed about the STARKIDS program and the accompanying study by the participating health insurance company. The project is also presented at different meetings of pediatricians by the study team. Additionally, a STARKIDS project website is launched with information about the study for potential families and pediatricians. Second, participating pediatric practices recruit families with children and/or adolescents with overweight/obesity: they go through their patient database to identify eligible children/adolescents and invite all eligible families to participate. Additionally, information material about the study provided by the study team is displayed in the practice (e.g., waiting room) to encourage eligible families to participate.

### Assignment of interventions: allocation

#### Sequence generation {16a}

The allocation sequence is randomly computer-generated.

Factors for stratification of participating pediatric practices are:Practice in an urban or rural area (according to postal code)Practice is a potential high recruiter or not (more than one participating pediatrician per practice or not)

Since practices are cluster-randomized, the participating families themselves are not allocated randomly but allocated through their pediatric practice.

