## Statistical methods

### Statistical methods for primary and secondary outcomes {20a}

For the analysis of both primary and secondary outcomes a frequency comparison *χ*^2^c tests accounting for dependencies among observations within clusters [67] as well as generalized estimation equations (GEE) approaches will be used. The latter regression models will incorporate adjustment for relevant baseline covariates as well as concurrent covariates. A dichotomous variable capturing membership in the control vs. intervention group will be included in these models to assess the treatment effect as well as—with interaction terms—differential effectiveness in subgroups.

Analyses are conducted using all observations with available data (intention-to-treat) as well as the per-protocol subset of observations with adequate consideration of potential differences in results between these two strategies. Maximal utilization of data from families that eventually drop out of the intervention program will be secured and adequate steps will be undertaken to obtain at least measurements of the primary outcomes from these families after participation discontinuation.

In addition, cost-effectiveness and cost-utility analyses are performed. Adjusted total costs per capita, QALYs, and differences in total costs and QALYs between the control and intervention group are calculated using mixed-effects linear regression models with robust standard errors adjusted for relevant covariates at baseline. To account for uncertainty with regard to costs and effects, nonparametric bootstrappings are performed. The cost-effectiveness acceptability curves of the intervention group are calculated based on the net benefit approach. Therefore, multilevel mixed-effects linear regressions are used based on the net monetary benefit for different willingness-to-pay (WTP) thresholds. A long-term perspective on the macrosocial added value of STARKIDS will be performed with the help of decision-analytic modeling or state-transition modeling.

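### Practices are randomised within two strata, but the cluster-adjusted chi-square test that the trial is powered on ignores them; if the strata are prognostic, that test is conservative and precision is lost

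*Protocol article*

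**What the plan says.** In Sequence generation {16a} the list introduced by "Factors for stratification of participating pediatric practices are" has two practice-level entries. One is "Practice in an urban or rural area (according to postal code"); the other is "Practice is a potential high recruiter or not (more than one participating pediatrician per practice or not"). Crossed, they form four cells.

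Statistical methods {20a} names two analyses for primary and secondary outcomes. The first is a set of chi-square "tests accounting for dependencies among observations within clusters". The second is GEE, of which it says: "The latter regression models will incorporate adjustment for relevant baseline covariates as well as concurrent covariates". Covariate adjustment is thus assigned to the regression models and not to the chi-square test. Neither description mentions the stratification factors, and the section does not say which analysis is the primary test.

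Sample size {14} is built on the chi-square test. With 750 analysed children in 100 practices and a cluster effect of 2, it considers differences of 14 points (27% against 13%) to 17 points (58.5% against 41.5%) and says that these "are detectable with a maximum type I error rate of 5% and minimal power of 80"%. It adds that cluster sizes vary widely.

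**The concern.** Stratified allocation balances the arms on the strata, so differences between strata contribute little to the true variance of the treatment contrast. A test that ignores the strata still estimates its variance as if they contributed in full. If the strata are prognostic, the interval is too wide, the test rejects less often than its nominal level, and some of the precision that the stratification bought is not used.

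This matters more here than in an individually randomised trial. Both factors act at practice level, and the planning cluster effect puts more than half of the variance of an arm mean at that level. The test affected is the one that the sample size rests on.

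**Working it through.** **Inputs from Sample size {14}:** 750 analysed children, 100 practices (7.5 per practice), cluster effect 2, maximum error 5%, the two pairs of proportions. **Assumed:** two-sided testing, 1:1 allocation, equal cluster sizes, a cluster effect of 2 that is true and includes stratum differences, and the share R of between-practice variance that the two factors explain. The documents give no value for R, so a range is shown.

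**1. The plan's own power figure.** Effective n per arm = 750 / 2 / 2 = 187.5. Power = Φ[(d√n − 1.96√(2p̄(1−p̄))) / √(p₁(1−p₁) + p₂(1−p₂))].
- 27% vs 13%: (0.14 × 13.69 − 1.96 × 0.566) / 0.557 = 1.45, so power is 92.7%.
- 58.5% vs 41.5%: (0.17 × 13.69 − 1.96 × 0.707) / 0.697 = 1.35, so power is 91.2%.

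The stated 80% holds as a minimum but is not reproduced as a point value. That is a separate matter and does not bear on the present point.

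**2. Share of variance between practices.** ICC = (2 − 1)/(7.5 − 1) = 0.154. The between-practice share of the variance of an arm mean is 7.5 × 0.154 / 2 = 0.577. With 10 per practice the ICC is 0.111 and the share 0.556.

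**3. Effect of ignoring the strata.** The true variance, relative to what the unstratified test estimates, is v = 1 − 0.577R. The standard error is too large by the factor 1/√v. Actual error = 2[1 − Φ(1.96/√v)].

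| R (assumed) | v | SE too large by | Actual error | Power of unstratified test where the adjusted test has 80% |
|---|---|---|---|---|
| 0% | 1.000 | 0% | 5.0% | 80.0% |
| 5% | 0.971 | 1.5% | 4.7% | 79.2% |
| 10% | 0.942 | 3% | 4.4% | 78.3% |
| 20% | 0.885 | 6% | 3.7% | 76.4% |
| 30% | 0.827 | 10% | 3.1% | 74.1% |

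Last column: Φ[(2.8016√v − 1.96)/√v], where 2.8016 = 1.96 + 0.8416.

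**4. Power on the plan's own inputs.** Take the worst row, v = 0.827, √v = 0.909. For 27% vs 13%, the unstratified test has Φ(1.45/0.909) = 94.5%, and the adjusted test has Φ((1.96 + 1.45)/0.909 − 1.96) = 96.3%. For 58.5% vs 41.5% the figures are 93.1% and 95.4%. Ignoring the strata therefore costs about two points, and power stays well above 80%.

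**5. Simulation checks.** In 20,000 stratified randomisations of 100 practices per scenario, where strata explained 5%, 10% or 20% of the variance of practice means, the unstratified test rejected 4.4%, 4.1% and 2.7% of the time under the null. The formula gives 4.4%, 3.9% and 2.8%. With strata in the model, rejection was 4.7% to 5.2% across all scenarios. A second simulation, with a binary outcome and variable cluster sizes, used an uncorrected robust variance. There the stratum-adjusted test rejected about 5.7% to 6.6% of the time.

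**The case against.** The strongest reply is that this is mostly detail that an article may leave elsewhere. Urban or rural location and number of pediatricians are baseline characteristics of a practice, so the GEE wording can include them, and the covariate list may sit in the full protocol or the SAP, neither of which is shown. That stands for the GEE models: it cannot be said that they omit the strata, only that this article does not name them. It does not stand for the chi-square test, which the article chooses, describes with clustering only, and uses for its power statement.

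A reader might infer that the stated error rate is violated. It is not. The article promises "maximum type I error rate of 5% and minimal power of 80"%, and a conservative test respects a maximum. A reader might also infer that the trial is underpowered. The planning calculation counted no gain from stratification, and step 4 leaves power at 93% or more for both stated differences even at the largest assumed R.

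The size of the loss also rests on assumption. Nothing in the documents says that either factor predicts weight change, and one was chosen for recruitment potential. With an assumed ICC of 0.05 the between-practice share falls to 7.5 × 0.05 / 1.325 = 0.28, and the excess in the standard error is roughly halved. The formula is for a linear mean, while the sample-size criterion is binary. All of this stands and limits the point to one of efficiency.

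Finally, adding strata alone does not secure a 5% test, as the second simulation shows. The remedy therefore needs a corrected variance.

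**Conclusion.** The point holds as a mismatch between design and analysis that may cost precision. The chi-square test behind the sample size ignores the strata within which practices are randomised, and the article does not commit the GEE models to them by name. For R from 0% to 30%, with the cluster effect of 2 taken as true, the actual error lies between 5% and about 3.1% and the standard error is between 0% and about 10% too large. There is no loss if the strata are not prognostic, and a negligible one if they are weakly so. It is an inexpensive improvement that should be made; the validity of the trial is not in question.

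**What to change.** State that the primary between-arm analysis is the GEE model with treatment arm, the two stratification factors (urban or rural; one or more than one participating pediatrician) and the baseline value of the outcome, with practice as the cluster and a small-sample-corrected robust variance. Keep the cluster-adjusted chi-square test as supportive, or stratify it by the same four cells.

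The cost is a sentence or two in the analysis plan. Both factors are known for every practice before allocation, and two extra parameters against about 100 clusters are negligible. Settling this before the outcome data are analysed also removes a later choice between two named analyses.

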#### Concealment mechanism {16b}

Not applicable, since pediatric practices need to know their allocation in order to receive the correct training for the study.

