### Trial design {8}

The STARKIDS study is a cluster-randomized controlled trial with two parallel study arms: The intervention group receives the new STARKIDS program whereas the control group receives treatment-as-usual (TAU). Both treatments are conducted in pediatric practices that are randomly allocated to either the intervention or the control condition. Participants are therefore cluster-randomized as their allocation depends on their practice being an intervention or a control practice.

Data is assessed at three measurement time points from participating pediatric practices as well as participating families:T0: baseline/inclusion in the studyT1: T0 + 12 months, end of step 1 of the STARKIDS programT2: T0 + 18 months, end of step 2 of the STARKIDS program

The STARKIDS intervention is hypothesized to show superiority over TAU at T1 and T2.

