### Who will take informed consent? {26a}

Informed consent of participating families will be obtained by participating pediatricians after informing about the study and answering families remaining questions. Information about the study and consent are given to parents as well as children and adolescents, age-appropriate information materials are provided for the following groups: parents/legal guardians, 6–11 years old children, and 12–17 years old adolescents. For families with a child under 6, only parents give informed consent. Pediatricians’ consent to participate in the study will be obtained by the study team.

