#### Implementation {16c}

The study team will enroll participating pediatric practices. The allocation of the pediatric practices is done by the evaluating site. Participating practices will recruit and enroll patients. Patients are automatically assigned to interventions depending on their respective pediatric practice being in the intervention or the control group.

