### Assignment of interventions: blinding

#### Who will be blinded {17a}

Due to the nature of the study, testing the STARKIDS intervention versus a control intervention, participating practices cannot be blinded to allocation. During recruitment of families, practices are asked not to reveal their allocation to potential participating families until families have decided on their participation.

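### Practices that know their arm identify, invite, consent and enrol families, and the rule against revealing the arm ends at the family's decision, not after T0

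*Protocol article*

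**What the plan says.** The practice is the unit of randomisation: "Participants are therefore cluster-randomized as their allocation depends on their practice being an intervention or a control practice" (Trial design {8}).

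Under Concealment mechanism {16b} the whole entry reads: "Not applicable, since pediatric practices need to know their allocation in order to receive the correct training for the study". Who will be blinded {17a} adds that "participating practices cannot be blinded to allocation", and that during recruitment "practices are asked not to reveal their allocation to potential participating families until families have decided on their participation".

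Families are found after practices have joined: "Second, participating pediatric practices recruit families with children and/or adolescents with overweight/obesity", and to do so "they go through their patient database to identify eligible children/adolescents and invite all eligible families to participate" (Recruitment {15}). The remaining steps stay in the practice: "Participating practices will recruit and enroll patients" (Implementation {16c}), and "Informed consent of participating families will be obtained by participating pediatricians after informing about the study and answering families remaining questions" (Who will take informed consent? {26a}).

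Under Primary outcomes, the second primary outcome in the hierarchy is the change in quality of life from baseline, reported by the child or adolescent and by the parent in an online questionnaire. The first, BMI-SDS, uses height and weight measured in the practice.

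**The concern.** Two separate protections are at issue.

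**Concealment at identification and enrolment.** {16b} treats concealment as impossible because delivery cannot be blinded. These are different things. A practice must know its arm before its medical assistants are trained. It need not know it before it draws up a list of eligible children. In a cluster trial, randomising practices balances practices. It does not balance the families within them if staff who know the arm influence who is found, judged eligible and persuaded.

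The arms also ask very different amounts of the staff. Five core trainings of 90 minutes come to 5 × 90 = 450 minutes per intervention family, against one session of about 30 minutes per control family (Intervention description {11a}). Staff facing the longer commitment could lean towards families they expect to persist.

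**Timing of T0.** Once the family has decided, the practice may tell it the arm. If the T0 questionnaire is completed later, hope or disappointment about the allocation can enter the baseline rating. That rating is the reference for the second primary outcome and a natural adjustment covariate. A baseline affected by the arm no longer does either job properly.

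**Working it through.** **Step 1: do practices know their arm while recruiting?** No sentence dates disclosure. {17a}, however, asks practices not to reveal their allocation during the recruitment of families, and that request has a purpose only if they already know it. {16b} claims no concealment at any stage. Knowledge during recruitment is therefore a firm inference. Knowledge at the moment of the database search is likely but not stated.

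**Step 2: who acts with that knowledge?**

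| Step | Done by | Section |
|---|---|---|
| Database search and invitation | Practice | {15} |
| Consent | Practice pediatrician | {26a} |
| Enrolment | Practice | {16c} |
| Allocation of practices | Evaluating site | {16c} |

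Only the last step lies outside the practice.

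**Step 3: how much discretion is there?** Age, BMI percentile and insurance programme are objective. Adequate German, severe systemic disease and severe psycho-social burden unrelated to weight need some judgement. The effort put into persuading a family is not governed by any criterion.

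**Step 4: is T0 placed before the reveal?** T0 is labelled baseline or inclusion in Trial design {8} and Outcomes {12}. Neither section orders consent, reveal and questionnaire, and {17a} ties the reveal to the family's decision only. The timeline figure was not available in the text read, so the actual order cannot be confirmed. The article permits T0 after disclosure; it does not say that this happens.

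**Step 5: the plan's own precision.** Sample size {14} gives 750 analysed and a cluster effect of 2, so the effective number is 750 / 2 = 375, or 187.5 per arm (1:1 assumed, as the ratio is not stated). A two-sided 5% pooled χ² test then has power of 92.7% for 27% vs 13% and 91.2% for 58.5% vs 41.5%. The stated minimum of 80% holds as a lower bound and is not in dispute here.

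**Step 6: what would a given bias do?** The bias sizes are assumptions and there is no true effect.

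- SE of a standardised difference = √(2/187.5) = 0.103.
- Rejection rate = Φ(−1.96 + b/0.103) + Φ(−1.96 − b/0.103).

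| Assumed imbalance b (SD of analysed score) | Rejection rate |
|---|---|
| 0 | 5% |
| 0.05 | 7.7% |
| 0.10 | 16.2% |
| 0.20 | 49.1% |

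On the responder scale of {14}, a 5-point gap due only to selective enrolment gives 26.7% rejection from a 13% base rate and 16.4% from 41.5%. These figures use an unadjusted comparison. Covariate adjustment would reduce them to the extent that the covariates capture the imbalance.

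**The case against.** The plan contains real safeguards. All eligible families are to be invited. Families are to be kept unaware until they decide, which addresses differential acceptance. A separate site allocates the practices, eligibility is largely objective, the GEE models adjust for baseline covariates, and forty monitoring visits are planned. These limit the problem, but a gap remains. Without a list fixed before disclosure, nobody can check that all eligible families were invited. The non-reveal rule is only a request and binds families' knowledge, not that of staff. Adjustment cannot reach unmeasured motivation.

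It can also be said that this is a condensed article and that the full protocol may order T0 before the reveal. That is fair. But {17a} states an explicit end point for non-disclosure, and that end point is too early as written.

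A further objection concerns direction. If knowing the arm moved quality-of-life ratings equally at T0 and T1, the shift would cancel in a change score. This stands: neither the sign nor the size of the bias is established. A baseline taken before disclosure is still preferable, because it does not depend on that cancellation and leaves the baseline unaffected by the arm.

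A reader might go further and infer that baseline weight is distorted by families' knowledge. The documents give no mechanism for this, since height and weight are measured in the practice. BMI-SDS is exposed mainly through who is enrolled.

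**Conclusion.** The point holds as a weakness in two stated rules. Staff who identify, invite, consent and enrol families are not concealed from their arm, and the reason given in {16b} supports disclosure before training only. Separately, the non-reveal rule in {17a} does not protect the T0 quality-of-life questionnaire.

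The first weakness bears on both primary outcomes through selective enrolment. The second bears mainly on quality of life.

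The size is unknown. A reader might take the 16% or 49% rejection rates as the trial's expected false-positive rate. The documents do not support that, because 0.1 and 0.2 SD are chosen for illustration and no passage gives a bias of any size. Nor do the documents show that selective enrolment occurred or that T0 follows disclosure. The conclusion rests on the inference from {17a} about when practices know their arm and on the absence of any stated order between T0 and the reveal. It is a correction that should be made because it is cheap and because lost concealment cannot be fully repaired in the analysis.

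**What to change.** 1. **Move the reveal point in {17a}.** Replace the end point at the family's decision with: *until the T0 measurements and T0 questionnaires are completed*. All practices can adopt this at once. The cost is a short delay before families learn their arm.

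2. **Revise {16b} for practices not yet told their arm.** The practice completes and date-stamps its database search and eligible list, held locally, before the evaluating site discloses the allocation. Training follows disclosure. Later additions, such as families responding to displayed material or becoming eligible, are allowed but flagged. Holding the list locally avoids sending children's data to the centre before consent. The cost is an earlier search and a short wait for the allocation. Family enrolment began on 1 April 2022, so this step cannot help practices that already know their arm.

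3. **Report anonymous counts by arm.** Give the numbers eligible, invited and accepted. This needs only a tally from each practice. It does not remove selection, but it makes differences between arms visible.
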